#### Necrotizing Enterocolitis

Necrotizing enterocolitis may be diagnosed at surgery, at postmortem or clinically and radiologically: at least one of the following clinical signs present: bilious gastric aspirate or emesis, abdominal distension, or occult or gross blood in stool AND at least one of the following radiological features: pneumatosis intestinalis, hepatobiliary gas, or pneumoperitoneum. Infants who satisfy the definition of NEC but at surgery or postmortem have a “focal gastrointestinal perforation” will not be coded as having NEC.

All diseased cases meeting the predefined case definition of NEC or LOS will have samples analyzed (expected total ~70–100 infants). Samples from up to 200 non-diseased cases will be selected to ensure sufficient coverage of intervention arms using matching algorithms and coverage of other clinical risk factors and outcomes. We will also analyze samples from non-diseased cases to determine microbiomic and metabolomic profiles between trials arms.

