### Overview of the SIFT and ELFIN Trials

Speed of increasing milk feeds trial and ELFIN trials are funded by the HTA and managed by the National Perinatal Epidemiology Unit Clinical Trials Unit, Oxford, UK.^3^ Both trials recruit very preterm infants (<32 weeks gestation) in the first few days after birth while receiving care on a neonatal unit. The trial interventions complete prior to hospital discharge, although follow-up for SIFT continues until 2 years corrected age. SIFT recruited 2,804 infants and is powered to detect a clinically important difference in disability-free survival at 2 years, as well as having adequate power to detect a difference in the rate of the key short-term outcomes NEC and LOS. Infants were enrolled when stable, tolerating some milk (but less than 30 ml/kg/day), and when the attending clinician was ready to start increasing the amount of milk feeds. Infants were randomized to increases in milk feeds of either 18 or 30 ml/kg/day. Infants from multiple pregnancies (twins, triplets, etc.) were corandomized to the same treatment arm. It was anticipated that the speed of milk feed increases would result in full feeds (defined as at least 145 ml/kg/day) being achieved about 4 days later in the slower arm. This affects the duration of central venous access and use of parenteral nutrition, although this was not mandated in the SIFT protocol and therefore is likely to affect two key risk factors for LOS. The speed of milk feed increases may also affect exposure to breast milk in the first few days of life, a further risk factor for both LOS and NEC. SIFT is a trial of comparative clinical effectiveness and recognizes the possibility that there might be competing outcomes, i.e., there may be opposing impacts on NEC and LOS between the two trial arms (15). Hence, the use of disability-free survival as an outcome that takes this possibility into account. In addition, if there are no differences in key clinical outcomes (including neurological development), then data collected for health economic analyses may determine which regime is adopted in clinical practice.

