## Procedures—Summary

We will
Recruit at least 480 infants from up to 10 neonatal units in the UK enrolling infants to ELFIN.Identify stored samples from infants recruited to SIFT (one site only).Collect a daily stool and urine sample from MAGPIE infants until hospital discharge (average duration 40–50 days) or transfer back to local neonatal unit.Retrieve any residual resected gut tissue of enrolled infants who undergo intestinal surgery.Identify samples which are the most:
*informative*—based on trial intervention and disease presence;*comprehensive*—consistency of daily sampling;*representative*—balanced for trial intervention and other key factors, e.g., gestation, breast milk exposure.Samples to be analyzed will include
*all diseased cases*: infants who meet the SIFT and ELFIN internationally agreed predefined case definitions of confirmed NEC or LOS following review at Blinded Endpoint Review Committee;*non-disease cases*: infants who do not develop NEC or LOS, selected using matching algorithms to ensure trial intervention and risk factor coverage.The samples analyzed will focus on the early postnatal period when trial intervention differences will be greatest: e.g., day 0—3, 6–8, 9–11, 13–15, and 20–22 in ~25–50 infants per trial intervention arm. While we aim for daily sampling we recognize this will not always be achieved due to the complexity of the NICU working environment, combined with the fact that many sick infants do not pass a stool every day. We will also analyze samples at additional time points as necessary to ensure a daily sample is analyzed for up to 7 days before diagnosis in all diseased cases and match these to non-disease controls.Analyze samples for

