
### Statistical Analysis

There are three major modeling issues that have to be addressed in this analytical pathway:
(i)the multivariate nature of the microbiome and metabolome, and data generated from immunohistochemistry;(ii)the longitudinal/developmental component in the neonate, which will lead to repeated measures of disease state and microbiome on the same individuals, and(iii)the interdependence and interactions between different predictors, which may have both direct and indirect effects on incidence and progression of disease.

The analytical approach used in this study will focus on modeling the relationship between putative risk factors, trial interventions, and incidence of NEC and LOS from longitudinal data capturing variation in both risk factors and disease through time, and the any differences in non-diseased cases between trial arms. We will use a progressive modeling strategy based on combining multivariate analyses of micro- and metabolomic immunological data, with mixed-effect modeling of outcome in relation to drivers of disease; and finally, mixed-effect SEM to quantify the importance of interacting factors and drivers. Specifically, we will
(i)quantify the impacts of individual risk factors in causing disease;(ii)quantify the effects of direct and indirect risk factors on disease;(iii)quantify the dynamics of pathogens, the neonatal microbiome, the immune response, and their impact on outcomes, and(iv)identify the impacts of trial interventions and clinical management on the drivers and disease.

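### Two sections place the comparison of trial arms in infants who never develop NEC or LOS: randomisation does not protect that contrast, and other sections state arm comparisons without the restriction

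*Protocol article*

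**What the plan says.** Two places name a population for comparing arms, and both name the non-diseased infants. Under Case Definitions of Disease, at the end of Necrotizing Enterocolitis: "We will also analyze samples from non-diseased cases to determine microbiomic and metabolomic profiles between trials arms". Under Statistical Analysis, the modelling is also to cover "any differences in non-diseased cases between trial arms".

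Procedures—Summary defines the non-disease group as "infants who do not develop NEC or LOS, selected using matching algorithms to ensure trial intervention and risk factor coverage". The Necrotizing Enterocolitis section caps it at 200 infants and adds "coverage of other clinical risk factors and outcomes" as a selection aim. Procedures—Summary also wants the analysed samples to be "balanced for trial intervention and other key factors, e.g., gestation, breast milk exposure". On SIFT, the trial overview says: "The speed of milk feed increases may also affect exposure to breast milk in the first few days of life". The background section on feeding rates goes further and says slower increases reduce that exposure.

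Elsewhere, arm comparisons carry no disease-free limit:
- Aims and Objectives: the first hypothesis and first outcome compare arms on gut microbiota and name no restricted population.
- Procedures—Summary: fixed early windows in about 25–50 infants per arm.
- Laboratory Procedures (stool and urine): metabolomic differences between arms.
- Plan for Interim Statistical Analyses: samples taken before disease onset, 7–10 days after starting lactoferrin or placebo, in up to 60 infants per group. These infants need not stay disease-free afterwards.

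**The concern.** Randomisation makes the arms comparable as randomised. Staying free of NEC and LOS is an outcome: ELFIN is powered for lactoferrin to lower LOS, and the trial overview says SIFT has adequate power for differences in NEC and LOS. If an intervention works, it changes which infants are left in the non-diseased group. A difference between arms in that group then mixes the effect on the microbiome with the effect on who remains.

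This matters because, of the three hypotheses, only the one on trial interventions rests on randomisation. The Summary justifies the study by pointing to residual confounding in observational work and to the need for trials to establish causation. A contrast restricted on outcome gives up part of that advantage. The protocol also leaves unclear which population serves the main arm comparison, and the interim population is less restricted than the one in Statistical Analysis.

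**Working it through.** The protocol gives no figure for this contrast, so there is none to reproduce. The steps below size the effect of the restriction for ELFIN.

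**Inputs.** LOS 18% vs 13% (Overview of the SIFT and ELFIN Trials). 480 infants and 70–100 disease cases (Sample Size Estimates). 50 infants per arm (upper end of the fixed-window range). The calculation uses LOS only and assumes the arms do not differ in NEC.

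**1. How many leave the comparison.** Overall 70/480 = 14.6% to 100/480 = 20.8%. By arm, on LOS alone, 82% of placebo and 87% of lactoferrin infants remain. With an assumed equal split of 240 per arm, that is 240 × 0.82 ≈ 197 and 240 × 0.87 ≈ 209.

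**2. Shift in the contrast.** Let D be the non-diseased minus the diseased mean of a microbial measure, taken as equal in both arms, and p the disease proportion.
- Arm mean = (1 − p) × non-diseased mean + p × diseased mean = non-diseased mean − pD.
- So non-diseased mean = arm mean + pD.
- Restricted contrast = all-infant contrast + (0.13 − 0.18) × D = all-infant contrast − 0.05 × D.

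The documents do not give D. Under assumed values:
- D = 0.5 SD: shift of 0.025 SD in size
- D = 1 SD: 0.05 SD
- D = 2 SD: 0.10 SD

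**3. Check with a different model.** Let LOS occur when a normally distributed liability passes a threshold giving 18% and 13%, and let the microbial score have correlation ρ with that liability (assumed 0.1–0.9). The mean score among non-diseased infants is μ − ρφ(c)/Φ(c), with Φ(c) = 0.82 or 0.87.
- No true difference between arms: the restricted contrast shows 0.008 SD (ρ = 0.1) to 0.069 SD (ρ = 0.9).
- A microbial effect that carries the whole LOS reduction: attenuation of 0.4% (ρ = 0.1) to 29.5% (ρ = 0.9). At ρ = 0.5, −0.422 SD becomes −0.384 SD, or 9.1%.

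So the restriction can create a small difference where there is none, or shrink a real one.

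**4. Against the precision of the study.** With 50 per arm the standard error is √(2/50) = 0.20 SD. The difference detectable with 80% power at two-sided 5% is (1.96 + 0.84) × 0.20 = 0.56 SD.

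**5. Breast milk.** The protocol's own text makes this exposure a possible consequence of the SIFT arm. Balancing SIFT samples on it can remove part of a route by which feed rate may act. The documents give no figure from which to size this.

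**The case against.** The best defence is that this is not the only arm comparison. The sentence in Necrotizing Enterocolitis begins by saying the analysis is additional, all diseased infants are assayed as well, and the sections listed above describe arm comparisons with no disease-free limit. A reader might infer that the first hypothesis as a whole loses its causal basis. The documents do not support that. What stands is that the two places naming a population both name the restricted one, and they do not agree with the rest.

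Four other strong readings also go too far:
- **Breast milk in ELFIN.** The protocol links this exposure to feed rate only. SIFT supplies around 100 stored-sample infants from one site, and nothing says that lactoferrin, a blinded additive to milk, changes breast-milk exposure. Balancing may also mean coverage rather than equalising the arms.
- **Completeness of sampling.** Procedures—Summary prefers consistently sampled infants and notes that "many sick infants do not pass a stool every day". That may limit generalisability, but nothing shows it differs by arm.
- **An effect lost completely.** If lactoferrin acted only by moving the 5% of prevented cases to the non-diseased state, the all-infant contrast would be 0.05 × D and the restricted one zero. This is a limiting case. At D = 1 SD, even the all-infant effect would need about 2 × (1.96 + 0.84)² / 0.05² ≈ 6,300 infants per arm to detect.
- **Bias toward no effect.** Step 3 shows it can go either way.

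It is also fair to say that the study is exploratory and that this is a condensed article. Detailed matching rules may sit in a fuller document. That does not answer the point, which rests on what the article states.

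**Conclusion.** The concern holds for the arm contrast stated in the Necrotizing Enterocolitis and Statistical Analysis sections. That contrast is restricted on a post-randomisation outcome that ELFIN is powered to change, and it does not match the arm comparisons in Aims and Objectives, Procedures—Summary and the interim plan. For the SIFT samples only, balancing on breast-milk exposure is a second instance of conditioning on a possible effect of the intervention.

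The size is modest: −0.05 × D, or 0.05 SD in size at an assumed D of 1 SD, which is about a quarter of the standard error with 50 per arm. This rests on the 18% and 13% LOS rates being realised, an equal D in both arms and no arm difference in NEC. The direction is not established. Severity is below must-fix; it is worth correcting because it concerns the one randomised question and the correction is cheap.

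**What to change.** In the Necrotizing Enterocolitis and Statistical Analysis sections:

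1. State that the main arm contrast uses all randomised MAGPIE infants with a sample in the fixed window, taken before any disease onset as in the interim plan, whatever their later NEC or LOS status. The pre-onset rule still drops infants whose disease starts before the window, so report their number by arm.
2. For this contrast, draw non-cases at random within arm by gestation strata. Otherwise weight them by their actual stratum-specific selection probabilities. One overall weight, (480 − 100)/200 = 1.90 to (480 − 70)/200 = 2.05, would not recover the cohort, because non-cases are picked by matching and risk-factor coverage.
3. Do not select SIFT samples for the arm contrast on breast-milk exposure.
4. Adjust the arm contrast for baseline factors only. Keep feed and antibiotic exposures, which the interim section lists as adjustment variables, for the disease models.
5. Keep the comparison in non-diseased infants as a labelled sensitivity analysis.

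The cost is wording, the weights and possibly a few fixed-window assays on stored samples from cases. No extra recruitment or sample collection is needed.

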### Laboratory Procedures—Stool and Urine

We will analyze bacterial DNA extracted from stool samples using our well-established protocols and 16S ribosomal RNA methods that are effective tools to explore the diversity of bacterial communities (24, 76, 77). We will conduct metabolomic profiling of stool and urine. Extraction of samples will be optimized for detection of SCFAs and samples processed using non-targeted and targeted high-resolution LCMS to generate metabolomic profiles that may indicate functional changes in the host and the gut microbiota. Our targeted approach will investigate known gut flora fermented products of complex carbohydrates, including SCFAs, acetates, amino acids, and carbohydrate fragments, which may be present in stool samples. Analysis of the stool metabolome reflects changes in gut microbial activity and may impact on host gut function such as changes in permeability. Our non-targeted approach will allow us to compare metabolomic differences between trial arms in order to define a metabolite pattern associated with sample groups that can be correlated with information on microbial diversity, health, or disease.

We have optimized a LCMS method based on C18 reverse phase chromatography coupled to a Q-Exactive high-resolution mass spectrometer validated on 100 mg of stool and has demonstrated the robust and reproducible detection of 10^3^ metabolites (28, 58). Identification of significant metabolites will be based on data-dependent tandem MS/MS and confirmed using standards. Analysis (see Statistical Analysis) will use modeling techniques to explore relationships between the microbiome and metabolome, and study interventions and disease. Examination of the urinary metabolome is more reflective of changes to the overall host (infant) metabolic state but may also reflect differences in absorption of compounds from the gut. Determining the metabolomic profiles between and within patients to complement the stool microbiome sequencing data will enable exploration of how the host, gut microbes, trial interventions, and other clinical factors may interact, and any downstream functional effects such as feed tolerance or growth. To supplement the metabolomic data, we will store samples so future studies can analyze urine and stool samples using assays for proteins such as calprotectin and iFABP that may provide additional diagnostic or mechanistic information (78–81).

Volatile organic compounds from stool samples will be analyzed by GCMS using well-established protocols for extracting and analyzing headspace gases. These methods are based on a CARB/PDMS SPME fiber, a Combipal sampler with a Peltier-cooler, and a Perkin Elmer Clarus 600 Gas Chromatograph with Clarus 600T Mass Spectrometer (82). The method is validated on as little as 50 mg of sample: sufficient to analyze ~40 compounds, which includes 8 different acids, particularly SCFAs, branched and linear, alcohols, and esters. Interpretation of fragment patterns will be undertaken against the current mass spectral NIST library, followed by manual visual inspection (82).

### Laboratory Procedures—Resected Gut Tissue

The MAGPIE study provides a unique opportunity to explore potential gut actions of feeding rate and lactoferrin in a small number of cases if NEC occurs. This may include immunomodulatory and anti-inflammatory actions mediated by modulating cytokine expression, mobilizing leukocytes into the circulation, and activating T-lymphocytes. Breast milk and lactoferrin enhance proliferation and differentiation of enterocytes and closure of enteric gap junctions (36). Tissue-based analyses will take place in two domains: (1) exploring the aberrant innate and adaptive immune mechanisms and (2) validating immune pathways or biomarkers identified by microbiomic or metabolomic profiling.

Immunohistochemistry will be performed using paraffin blocks cut into 4 µm sections for staining using a Discovery XT auto-stainer (Ventana Medical Systems, Inc., Tucson, AZ, USA). Slide images will be acquired using the Vectra 3.0 Automated Quantitative Pathology Imaging System (Perkin Elmer, Waltham, MA, USA), using techniques optimized by our group at Newcastle. Antigens of interest will be quantified digitally. Leukocyte infiltrates associated with NEC will be identified using antibodies to several epitopes, for example, markers of inflammatory cell subsets, cellular proliferation, cytotoxic granule expression, transcription factors, or cytokines. Many of these antibodies have been previously optimized for intestinal tissue by the team at Newcastle, and new antibodies will be optimized as required informed by data generated in other work strands of this project. Staining of “healthy” resection margins from the same patient will be undertaken where possible and control analyses will be performed by use of matched non-NEC control tissue collected from MAGPIE infants, supplemented if needed by further samples from the Newcastle upon Tyne Hospitals biorepository (e.g., cases of spontaneous neonatal perforation). Targeted exploratory histology will validate immune mechanisms highlighted by metabolomics or microbial assays, and *in situ* hybridization may also be performed to identify transcription of relevant immune pathways identified by VOC, microbiomic, or metabolomic profiling.

### Sample Size Estimates

Sample size requirements for each element of this study have been evaluated and are based on both published data and practical/logistical aspects from our existing work and that from other published studies. These considerations include
The duration, estimated start time, and recruitment rate for ELFIN, along with the estimated start date for MAGPIE and logistical issues in establishing recruitment from 10 hospital sites.The trial efficacy and disease event rate will not be known until the main trial completes. The incidence of NEC (Bell stage 2 or greater) is expected to be 5–10% and for LOS <20%, and some infants will have both diseases. Recruiting 480 infants will identify between 70 and 100 “disease” cases, 10–20 cases requiring gut surgery, and provide well sampled “non-diseased” infants with varying clinical risk factors, exposures, and outcomes.VOC analysis may identify several individual compounds; in our recent paper publishing the methodology, we show that on average 31.3 ± 10.5 (mean and SD) VOCs were identified per sample (82). At a power of 80%, and two-sided significance at the 5% level, we would need 50 infants per trial intervention group to show an increase in 5 VOCs. The SD for each sample was 2.9 ± 1.3 compounds and on average 90% of the VOC abundances showed a coefficient of variation smaller than 30%. Our data also showed in a study of 13 infants, which VOC number in healthy neonates significantly increased with age (0.49 extra VOCs per day 95% CI 0.12–0.86), a trend not seen in those who developed NEC (64).Microbiomic data complexities means that the sample size necessary to evaluate the actions of different interventions and the incidence of disease is dependent on effect size, the number of interacting factors, and their correlation. For a power of 80% to detect a 50% difference in community profile patterns arising from a categorical descriptor of microbial community variation, using a two-sided test at a significance level of 5%, the study needs ~200 samples. In our previous studies (1) 12 twin pairs analyzed (gut microbial profiling) using PLS-DA showed highly significant correlations between pairs (53) and (2) examination of 136 samples from 32 patients (*n* = 20 NEC or LOS) showed significant differences (*p* = 0.002) in microbiomic patterns between diseased and healthy individuals (24).Using immunohistochemical data from our group (83), and assuming that any differences between disease and control will be greater than those in healthy individuals, and using a two-sample *t*-test, our proposed sample size of 20 would give 80% power to detect a difference of 0.66 (66%) in cells/crypt cross section at a significance level of 5% and an approximated SD of 0.5 (50%).Mixed-effects models, which we propose for modeling the direct effects of the microbiome on disease risk, are economical with power because the residual variance of these models is smaller since some of it is accounted for in the random effect. Using the method by Cohen (84), we calculate that a GLM would have a power of 82% with 10 predictors and 50 for a “large” effect size (*f*^2^ = 0.35, *R*^2^ = 0.51) at the 5% level of significance, and a power of 47% for a “medium” effect size (*f*^2^ = 0.15, *R*^2^ = 0.36) at the 5% level of significance. With *n* = 100 the calculated powers are 99% for a large effect size and 74% for a medium effect size. Including random effects in the GLM would increase power at the same effect size or conversely permit smaller effect sizes at the same power. The power analysis of an SEM is altogether more complex because it relies on the goodness-of-fit criteria selected for the model. Power at the model level may be low when there are few model degrees of freedom even for a reasonably large sample size; requiring greater than 100 samples if there are fewer than 20 model degrees of freedom (85). We will supplement these models where needed using a Bayesian SEM approach.

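### The VOC sample size does not follow from its stated inputs: with one sample per infant, 5 VOCs needs about 70 infants per group, not 50

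*Protocol article*

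**What the plan says.** The VOC item under Sample Size Estimates reports from earlier methodological work that "on average 31.3 ± 10.5 (mean and SD) VOCs were identified per sample". Setting power at 80% with a two-sided test at 5%, it then concludes: "we would need 50 infants per trial intervention group to show an increase in 5 VOCs". A second, much smaller SD follows: "The SD for each sample was 2.9 ± 1.3 compounds". The item mentions no loss of samples, covariate adjustment, repeated-measures gain or unequal allocation.

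The Procedures summary says that analysis will concentrate on the early postnatal period. It gives five example day windows and a number of about "25–50 infants per trial intervention arm". Stool VOC by GCMS is one of the analyses then listed.

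**The concern.** The sentence gives everything needed for a two-sample comparison of means: SD, difference, significance level, sidedness, power and group size. These values do not agree with one another. With SD 10.5, a difference of 5 is a standardised difference of 0.476, and 50 per group is too few to detect that with 80% power.

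This is the only sample-size item that gives a number of infants per trial arm, so a reader will use it to judge how informative the VOC comparison between arms can be. The abstract expects mechanistic results to be especially useful where the main trials show no clear effect. A null VOC result read as coming from a comparison with 80% power, when the stated inputs give about 65%, would carry more weight than it should. The figure of 50 is also the top of the planned range of infants per arm, so the number assayed may stop at or below it.

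**Working it through.** **Inputs, all from Sample Size Estimates**
- SD: 10.5 VOCs per sample, the only between-sample SD given and the one stated just before the claim.
- Difference: 5 VOCs, so the standardised difference is 5/10.5 = 0.476.
- Test: "two-sided significance at the 5% level"; power 80%.
- Groups: equal, "50 infants per trial intervention group".
- My assumption: one sample per infant. The document does not state this.

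**Attempt to reproduce 50**

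n per group = 2 × (1.96 + 0.8416)² × (10.5/5)² = 2 × 7.849 × 4.41 = 69.2, so 70. The exact two-sided t-test gives 70.2, so 71. The stated 50 is not reproduced.

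**Power and detectable difference (exact t-test, SD 10.5)**

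| Infants per group | Power for 5 VOCs | Difference detectable with 80% power |
|---|---|---|
| 25 | 37.8% | 8.5 VOCs |
| 50 | 65.5% | 5.9 VOCs |
| 60 | 73.5% | 5.4 VOCs |
| 71 | 80.4% | 5.0 VOCs |

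The normal approximation gives 39.1% and 66.3% power at 25 and 50 per group, with detectable differences of 8.3 and 5.9 VOCs.

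**Alternatives tried, to see whether any yields 50**
- One-sided 5%: 55 to 56 per group. This also contradicts the stated two-sided test.
- SD 2.9, the other SD in the item: 6 per group (7 by t-test).
- SD 10.5 with the 2.9 component removed, √(10.5² − 2.9²) = 10.09: 64 per group. With it added, 10.89: 75 per group.
- Mann–Whitney test, asymptotic efficiency 0.955: 70/0.955 = 73.3, so about 74 per group.
- Allocation 2:1: 52 in the smaller group, but the text gives one number for each group.
- Difference of 6 instead of 5, SD 10.5: 49 per group (49.1, so 50, by t-test). This matches but is not the stated difference.
- Difference of 5 with 50 per group: needs an SD of about 8.8 to 8.9, which the document does not give.

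**Repeated samples (illustration)**

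If each infant contributes the mean of m samples with within-infant correlation ρ, the SD becomes 10.5 × √[(1 + (m − 1)ρ)/m]. The document gives no ρ, so a range is shown. With m = 5:

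| ρ | SD of infant mean | Power at 50 per group | Power at 25 per group |
|---|---|---|---|
| 0.4 | 7.57 | 90% | 63% |
| 0.5 | 8.13 | 86% | 57% |
| 0.6 | 8.66 | 82% | 52% |
| 0.63 | 8.81 | 80% | 50% |
| 0.8 | 9.62 | 73% | 44% |

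**The case against.** The strongest objection is that the SD is per sample while the stated number is infants. The procedures foresee about five early windows per infant, the Statistical Analysis section names repeated measures as a central modelling issue, and the sample-size section notes that random effects reduce residual variance. If five samples per infant were averaged, 50 per group would reach 80% power for any within-infant correlation up to about 0.63. This stands as a possible explanation. It does not rescue the sentence, which invokes no repeated sampling and gives no correlation. The remark on random effects belongs to a separate item, on modelling microbiome effects on disease risk.

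A reader might also infer that the study's VOC comparison has only 38% power, because the procedures allow 25 infants per arm. The document does not support that. The range is approximate, offered as an example, and covers all laboratory platforms and several time windows. Under Case Definitions of Disease, samples from all diseased infants (about 70 to 100) and up to 200 non-diseased infants are to be analysed, with the latter also used to compare arms. The interim plan allows up to 60 per group for the microbiome. These are ceilings and do not guarantee 70 per arm, but they prevent 25 from being read as the VOC sample size. The 38% is therefore conditional on 25 infants per arm and one sample each.

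A further objection is that little depends on the figure. VOC count is not among the outcomes listed under Aims and Objectives, the target of 480 is linked to the expected number of disease cases, and the interim decision uses microbial community differences. This stands and limits the severity.

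**Conclusion.** The stated sample size is wrong on its own inputs. With SD 10.5, a difference of 5 VOCs, a two-sided 5% level, 80% power and one sample per infant, 70 to 71 infants per group are needed. The plan's 50 is about 30% short (1 − 50/71 = 0.30). At 50 per group, power is about 65%, so the type II error is about 35% instead of 20%, and the difference detectable with 80% power is about 6 VOCs.

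This rests on two assumptions: that 10.5 is the SD that entered the calculation, which its position implies but the text does not say outright, and that each infant contributes one sample. It shows that the sentence cannot be reproduced. It does not show that the final VOC analysis will be underpowered, since that depends on how many infants and samples are assayed and on a correlation the document does not give.

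Severity is moderate: a checkable figure needs correcting, in an exploratory study where neither recruitment nor the interim decision depends on it.

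**What to change.** Restate the sentence in one of three ways:
- about 70 infants per group for an increase of 5 VOCs;
- 50 infants per group for an increase of about 6 VOCs;
- if repeated samples per infant were assumed, give the number of samples and the within-infant correlation, and recompute.

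In the Procedures summary, or beside the corrected sentence, state the VOC difference detectable with 80% power at the number actually assayed. With one sample per infant this is about 5.9 VOCs at 50 per arm and about 8.5 at 25. For the SIFT samples, from around 100 infants and so about 50 per arm if evenly split, it is about 6 VOCs.

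These are wording changes and cost nothing in recruitment. Assaying about 70 infants per ELFIN arm, from samples the study already collects, is optional. It is not free: going from 50 to 71 adds 21 infants per arm and going from 25 adds 46. At five windows each, that is roughly 105 to 230 extra GCMS samples per arm, and more if sequencing and LCMS are extended to the same infants.
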